### Relevant concomitant care permitted or prohibited during the trial {11d}

We make no restrictions on concomitant care or interventions during the trial.

### Provisions for post-trial care {30}

We have no plan for ancillary or post-trial care or compensation for the participants. This is a pragmatic trial comparing widely used medications.

### Outcomes [12]

#### Primary outcome

Clinical cure 10 days (+/− 2 days, i.e. weekends) after antibiotic treatment completion defined as being alive with absence of fever (≥ 38.3 °C) and resolution of, or return to non-infected baseline of, urinary tract symptoms (as defined in inclusion criteria) without hospital readmission (for UTI symptoms) or additional antibiotic treatment (for UTI symptoms) based on a structured telephone interview performed by a centralised allocation-blinded study nurse.

#### Secondary outcomes

Participants’ perception of treatment tolerability on a 1–10 scale.Early study drug discontinuation.Additional antibiotic subscriptions (for UTI) within 28 days from randomisation.Proportion of patients re-admitted to hospital (due to UTI symptoms) within 28 days from randomisation.Drug-related serious adverse events within 28 days from randomisation.All-cause mortality within 28 days from randomisation.Growth of EPE (phenotypically same species) in urine culture (10^3^ CFU/mL) 10 +/− 2 days after antibiotic treatment.Growth of EPE or carbapenemase-producing bacteria in faecal cultures 10 +/− 2 days after antibiotic treatment.

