#### Secondary objectives

To compare participants’ perception of treatment tolerability on a 1–10 scale.To compare the incidence of early study drug discontinuation between groups.To compare the incidence of additional antibiotic subscriptions (for UTI) within 28 days between groups.To compare re-admission to hospital (due to UTI-related symptoms) within 28 days between groups.To compare the incidence of drug-related serious adverse events (SAE) within 28 days between groups.To compare the all-cause mortality within 28 days between groups.To compare the recurrence prevalence of EPE (phenotypically same species) in urine cultures 10 +/− 2 days after antibiotic treatment between groups (i.e. microbiological cure).To compare the prevalence of EPE or carbapenemase-producing bacteria in faecal cultures 10 +/− 2 days after antibiotic treatment between groups.

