## Assignment of interventions: blinding

### Who will be blinded {17a}

Trial participants and in-patient care providers will not be blinded to interventions in this pragmatic trial. Neither will the treating physician who assesses secondary endpoints 2-8. However, the central outcome assessor of the primary outcome will be blinded to interventions, as will the trial investigators, data analysts and author group. When data is extracted from the REDCap database, the allocation will be coded as “1” and “2” and the Code Key will only be revealed after statistical evaluation of the primary and secondary endpoints.

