## Data collection and management

### Plans for assessment and collection of outcomes {18a}

Baseline data and allocation will be entered into the REDCap database using a short and study-specific electronic case report form (eCRF) directly when assessing eligibility and assigning allocation by the physician who recruited the participant. The trial investigators will instruct a limited number of physicians at participating centre how to access and fill out the eCRF and provide a step-by-step guide and contact information for technical assistance. The primary outcome and the secondary outcomes 2-4 will be assessed using a semi-structured interview with a trial-specific guideline and entered into a separate part of the REDCap eCRF. The first 10 participants’ interview responses will be checked for conformity between at least two study nurses. The remaining secondary outcomes will be assessed retrospectively through medical chart review and from microbiological results by the recruiting physician at 30–60 days after the patient was allocated and then entered into a final separate part of the eCRF. The retrospective chart review will also serve as a sensitivity analysis to the telephone interview for the primary outcome and the secondary outcomes of early drug discontinuation and further antibiotic prescription. A copy of the REDCap eCRF (English) and semi-structured interview guideline (Swedish) can be sent on request.

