### Interim analyses {21b}

An interim analysis will be performed once half of the patients have been included (*n* = 165). Blinded data will be delivered by an independent statistician to the Data Monitoring Committee (DMC) who will then provide an allocation-blinded recommendation to the trial investigators whether to continue, hold or terminate the trial prematurely. The recommendation is based on safety and futility. Safety is based on three parameters, the number of possibly related serious adverse events, the number of early study drug discontinuations and the number of deaths within 28 days. It is difficult to provide fixed stopping criteria for safety since these events are expected to be very few, and the DMC have to assess frequency, severity and possible relationship to the study drug and give their best advice accordingly. Futility is defined as less than 5% probability of finding non-inferiority in the final analysis based on conditional power simulations as suggested by Bratton et al. [48]. The trial investigators will make the final decision whether to terminate the trial and will have to provide a written account to explain if they do not follow the recommendation from the DMC.

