### Adverse event reporting and harms [22]

Because the trial evaluates well-known and well-used drugs, we have an agreement with the Swedish Medical Products Agency to primarily focus on severe adverse events (SAE, see definition in Table 4 below). The recruiting trial physician will have the primary responsibility to identify and report any SAE from allocation and until day 28. If the telephone interviewer suspects an SAE, they are required to contact the recruiting physician by telephone the same day. If the recruiting physician identifies an SAE, then he or she is required to email the investigators as soon as possible or at latest within 24 h. If a connection between the SAE and the study drug cannot be ruled out, the investigators are responsible to report to the sponsor within 24 h. The sponsor is responsible for ensuring that a serious unwanted and unexpected incident or reaction, which is suspected to be related to the study drug (SUSAR = suspected unexpected serious adverse reaction) is reported to the Medical Products Agency ([contact]) on a CIOMS form. SUSARs that are life-threatening or fatal are reported within 7 days to the Medical Products Agency and the Ethical Review Board, and other SUSARs are reported within 15 days. In this study, the Medical Products Agency registers SUSAR in the European trial module EudraVigilance. As long as the trial is ongoing, a safety report will be compiled once a year and reported via EudraCT to the Medical Products Agency.

**Table 4 Tab4:** Definition of adverse events

Intensity of incident	• Mild does not affect the patient's normal functions • Moderate affects the patient's normal functions to some extent • Severe affects the patient's normal functions to a great extent
Assessment of the connection between incident and study drugs	• Not (unlikely) related to the study drug: there is very little or no possibility that the study drug has caused the unwanted event. • Possibly related to the study drug: the association between the adverse event and the study drug is unknown but there is no other clear cause for the symptoms. • Probably related to the study drug: a reasonable temporal relationship exists between the adverse event and the study drug. Based on the investigator's clinical experience, the association is considered probable.

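### The only between-arm comparison of SAEs counts just those judged drug-related by physicians who know the allocation, so the comparison of non-fatal SAEs can be biased in either direction

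*Protocol article*

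**What the plan says.** Two serious-harm outcomes stand next to each other in the protocol article's Secondary outcomes: "Drug-related serious adverse events within 28 days from randomisation" (the fifth in the list) and "All-cause mortality within 28 days from randomisation" (the sixth). The Secondary objectives make both of them between-group comparisons: "To compare the incidence of drug-related serious adverse events (SAE) within 28 days between groups" and "To compare the all-cause mortality within 28 days between groups". Section {20a} analyses both by GEE, reported as a risk difference with a 95% confidence interval. No comparison of all SAEs irrespective of cause is listed.

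On who judges outcome 5, section {18a} first gives the primary outcome and secondary outcomes 2 to 4 to the interview, then states: "The remaining secondary outcomes will be assessed retrospectively through medical chart review and from microbiological results by the recruiting physician". Section {17a} lists who is not blinded and adds: "Neither will the treating physician who assesses secondary endpoints 2-8". Section {16c} has the enrolling physicians assign the intervention themselves.

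Table 4 grades relatedness as unlikely, possible or probable. The middle grade applies when "the association between the adverse event and the study drug is unknown but there is no other clear cause for the symptoms". The top grade rests on a plausible time course and the investigator's experience.

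The Interim analyses section {21b} names three safety parameters. The first is "the number of possibly related serious adverse events"; the others are early study drug discontinuations and deaths within 28 days.

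**The concern.** An outcome defined by causal attribution depends on two things: how often the event happens and how often the assessor ascribes it to the drug. When the assessor knows the arm, the second can differ between arms even if the first does not.

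That is plausible here. The background section says that clinical trials of the combination in febrile UTI are lacking, while section {6b} presents the oral comparators as international standard treatment. A physician might ascribe an event more readily to the novel combination, or less readily out of confidence in its familiar components. The protocol does not settle which.

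The filter can also hide real differences. The abstract and background name fewer nosocomial infections as a hoped-for benefit of the intervention. A serious infection acquired during prolonged intravenous or hospital care meets the Table 4 definition of an SAE, but need not be judged related to the drug, and would then drop out of outcome 5.

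At stake is whether the reported comparison of non-fatal SAEs reflects what happened to patients or partly reflects how physicians labelled it.

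**Working it through.** The point turns mainly on how the sections fit together. The protocol states no SAE rate or attribution share, so there is no figure of its own to reproduce.

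**Sections side by side**

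1. Is the SAE outcome filtered? Yes. Both the objective and the outcome are limited to drug-related events.
2. Is the filter applied with knowledge of the arm? Yes. Sections {17a} and {18a} both give outcome 5 to a physician who is not blinded. These sections disagree on who assesses outcomes 2 to 4, and {17a} calls the trial investigators blinded while Table 4 appeals to the investigator's experience. Neither ambiguity changes the reading for outcome 5.
3. Is there a safeguard? No blinded adjudication of relatedness is described. The blinded central assessor covers the primary outcome and the interview items only.
4. Is the cut-off fixed? No. The outcome says drug-related, {21b} refers to possibly related events, and {17b} refers to possibly or probably related events.
5. Are unfiltered data collected? Yes. The section on adverse event reporting requires every SAE between allocation and day 28 to be identified and reported, and Table 4 defines seriousness without reference to cause.
6. What serious harm is compared without drug attribution? All-cause 28-day mortality, and hospital readmission limited to UTI symptoms. Nothing else in the list covers non-fatal serious harm.

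**Illustration of size (all inputs assumed)**

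Let r be the true SAE risk, equal in both arms, and let a₁ and a₂ be the shares of SAEs judged drug-related in the two arms. Then

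apparent risk difference = r × (a₁ − a₂).

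| r | 50% v 30% attributed | 60% v 20% attributed |
|---|---|---|
| 5% | 0.05 × 0.20 = 1 point | 0.05 × 0.40 = 2 points |
| 10% | 0.10 × 0.20 = 2 points | 0.10 × 0.40 = 4 points |
| 15% | 0.15 × 0.20 = 3 points | 0.15 × 0.40 = 6 points |

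The sign depends only on which arm has the higher attributed share. If SAEs are identified equally in both arms, the difference in all SAEs is zero in every row.

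In patients, with 330 / 2 = 165 per arm and the 50% v 30% shares:

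- r = 5%: 165 × 0.05 × 0.50 = 4.1 against 165 × 0.05 × 0.30 = 2.5.
- r = 15%: 165 × 0.15 × 0.50 = 12.4 against 165 × 0.15 × 0.30 = 7.4.

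At the interim (165 patients in total, so about 82.5 per arm) these counts halve, to about 2.1 v 1.2 and 6.2 v 3.7. Section {21b} expects safety events to be very few and sets no fixed safety stopping criteria, so a few attribution decisions could colour what the committee sees on that parameter.

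**The case against.** A reader might infer that drug-related SAEs are the only serious harm compared between arms, or that the whole safety comparison and everything the Data Monitoring Committee sees has passed through a biased filter. The protocol does not support that.

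- All-cause 28-day mortality is a stated between-group comparison and an interim parameter, and needs no judgement of relatedness.
- Readmission for UTI symptoms is compared without drug attribution.
- Two of the three interim parameters, early discontinuations and deaths, need no relatedness judgement.
- Section {21a} has the committee informed of SAEs every half year with no stated limit to related events. It may ask for more SAE monitoring or for unblinding, and {21b} asks it to weigh possible relationship itself.

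Other arguments limit the point further. The Sample size section calls the secondary objectives exploratory, and the non-inferiority claim rests on clinical cure. The components are described as well known and widely used, so differential attribution is possible but not shown. A count of all SAEs is not free of knowledge of the arm either, since the same unblinded physicians identify and report the events.

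Finally, one can say that a table of all SAEs by arm belongs in the analysis plan, which is not shown. This last argument does not dispose of the matter. The protocol does not leave the choice open: it states which SAE outcome is compared, and who judges it. A further table would not change that outcome or the interim parameter. The other arguments stand, and they narrow the point to non-fatal SAEs.

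**Conclusion.** The point holds for the comparison of SAEs, and chiefly for non-fatal ones. Outcome 5 and one of the three interim safety parameters depend on a subjective attribution made with knowledge of the arm, with a cut-off that is worded in three ways. Apart from mortality and UTI-related readmission, no comparison of serious harm free of drug attribution is listed. The plan could be followed exactly and still yield a difference, or mask one, through attribution alone.

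Neither the direction nor the size can be determined from the protocol. The 1 to 3 points (up to 6 with the wider gap in attributed shares) rest on assumed SAE risks, assumed shares, equal true risk and equal identification of SAEs in both arms. They show what is possible and are not an estimate. The primary non-inferiority conclusion is not affected. This is worth correcting because the change is cheap, not because it endangers the trial.

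**What to change.** Three changes to wording:

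- Add any SAE within 28 days of randomisation, regardless of relatedness, as a compared secondary safety outcome, reported as a risk difference with a 95% confidence interval like the other binary outcomes.
- Add the same count to the interim safety parameters, given to the Data Monitoring Committee by coded arm.
- Keep drug-related SAEs alongside as supportive, with one relatedness cut-off used in the outcome list, {17b} and {21b}, and a statement of who makes the final assessment.

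No new data collection is needed, because all SAEs are already to be reported from allocation to day 28.

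The change has costs. The broader outcome is less specific to the drugs. It overlaps with UTI readmission, which already counts as failure in the primary outcome and is secondary outcome 4. It may also include stays prolonged by intravenous control treatment, since Table 1 expects about 40% of controls to receive ertapenem and Table 4 counts an extended hospital stay as serious. These are reasons to report both outcomes rather than replace one with the other. Because SAE identification stays unblinded, the change reduces attribution bias but does not remove every effect of knowing the arm.

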### Participant timeline [13]

The trial will end after 28 days from study recruitment (see Table 3 below). Any additional care for the trial participants once their participation in the trial has ended, where it differs from what is normally expected according to the medical condition of the clinical trial participant, will be managed according to routine care within Swedish healthcare. All documents will be stored for a minimum of 25 years after the trial has ended.

**Table 3 Tab3:**
[figure not shown]
Participant timeline

*PAC pivmecillinam and amoxicillin/clavulanic acid, TMX trimethoprim-sulfamethoxazole*

^*****^This refers to a sensitivity analysis for the primary outcome using retrospective medical journal review by the treating physician

^†^If information from the telephone interview assessor and the medical chart review assessor are divergent, we will always choose the conservative conclusion and stipulate failure (i.e. 1/0 1)

## Sample size {14}

We expect a clinical cure rate of 93%, based on previous trials on antibiotic efficacy in febrile UTI exploring similar primary outcomes [37, 41]. We have chosen a classic absolute non-inferiority margin of 10% in accordance with the U.S. Food and Drug Administrations (FDAs) recommendation on developing new drugs for complicated UTIs [43]. We consider this to be suitable considering the low severity of all aspects of the composite primary endpoint except for 28-day mortality which we will evaluate specifically as a secondary endpoint and in the interim analysis. When using a one-sided alpha of 2.5% and performing a statistical simulation of 300 enrolled patients in 30 clinics with an intraclass correlation coefficient of 0.1 and generalised estimated equations (GEE) comparison between two groups with a random intercept for site as the primary analysis we reach 90% power. We plan on recruiting 330 patients to allow for 10% loss to follow-up. The study is not powered to infer non-inferiority between the intervention and any single antibiotic in the control group, but only towards the control group as a whole. The secondary objectives should be considered exploratory and are not based on sample size calculations.

### Recruitment {15}

We aim to establish a surveillance or alert system at each microbiological department of participating centres so that all individuals with an EPE-positive urine and/or blood cultures goes through an initial screening for eligibility (i.e. in-patient and susceptibility to mecillinam and susceptibility to at least one of ciprofloxacin, TMX or ertapenem). If preliminarily eligible, the microbiologist will inform the locally recruitment responsible infectious disease physician who will then screen the remaining inclusion and exclusion criteria. Participants can also be recruited directly by an infectious disease physician at each site if they find a patient that is eligible and was not detected by the surveillance system.

We estimate that recruitment of 330 participants will take 3 to 4 years based on the following unpublished data. There were 190 EPE-positive cultures from 130 adults in Region Västmanland (280,000 inhabitants), Sweden, in year 2020. This corresponds to 46 persons per 100,000 inhabitants per year. The catchment area for the eight sites that have so far agreed to recruit patients adds up to just above 2 million persons. If we assume that one in five persons with a positive EPE-culture is eligible for the study and one in two eligible persons can be recruited, it will take 3.6 years to complete recruitment for the trial.

## Assignment of interventions: allocation

### Sequence generation {16a}

We will use a computer-generated blocked random number sequence with stratification for sex and site. We have chosen to stratify by sex because of diverging results in some previous trials for males [37] and females [41]. We are not certain that this represents a true relationship, but it is something that we would like to evaluate as a fixed effect in the primary analysis and hence balance in the allocation sequence [44]. The sequence and block size will be unavailable to those who enrol participants and to the trial investigators.

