#### Treatment duration

A 7-day course of ciprofloxacin has been shown to be non-inferior to a 14-day course in women in an RCT [37]. There is retrospective data indicating that a 7-day course may also be adequate for trimethoprim–sulfamethoxazole [38] but data from randomised trials are lacking and in practice a 10-day course in often used [39]. In men, a 2-week course of ciprofloxacin was non-inferior to a 4-week course [40]. In a more recent trial, a 7-day course of ciprofloxacin was inferior to a 14-day course of ciprofloxacin in short-time follow-up (10–18 days) but not in long-term follow-up (70–84 days post treatment) [41]. In a randomised trial of afebrile and haemodynamically stable patients with gram-negative bacteraemia where 47% were men and 68% had UTI, 7 days of antibiotics was non-inferior to 14 days [42]. In clinical practice [28] and for the purpose of our study, we consider a total treatment duration of 10 days to be reasonable for all drugs except ciprofloxacin in women where 7 days have been proved to be equally effective [37].

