## Statistical methods

### Statistical methods for primary and secondary outcomes {20a}

The primary outcome will be analysed between two groups using generalised estimated equations (GEE) using an identity link and binomial family [47], with site as a random effect and sex as a fixed effect. The result will be presented as risk difference with 95% confidence interval. We will state non-inferiority if the lower bound confidence interval does not stretch below −10% risk difference. The first secondary outcome on patients’ perception (ordinal 1–10 scale) will be analysed using a non-parametric Mann Whitney *U* test. The remaining secondary outcomes (all binary) will also be analysed using GEE and reported as a risk difference with 95% confidence interval. Risk differences will be presented in a forest plot. If the telephone interview and the retrospective review report different parameters for the primary outcome (e.g. the patient does not report additional antibiotic prescriptions for UTI, but such prescriptions are identified in the medical chart review), we will always choose the conservative option and consider this a failure.

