### Methods for additional analyses (e.g. subgroup analyses) {20b}

We will perform five sensitivity analysis to the primary outcome analysis. One will add a fixed effect (“adjust”) for the number of days of intravenous antibiotics (as a continuous variable) prior to allocation in addition to the baseline GEE model with a fixed effect for sex and a random effect for site. Secondly, we will perform an unadjusted analysis without fixed or random effects. Third, we will also analyse and report the primary outcome based on retrospective chart review versus results from the primary telephone interview. Fourth, we will also perform and report the primary outcome analysis results based on subgroups for the three different control drug allocations (i.e. ciprofloxacin, TMX and ertapenem). Lastly, we will analyse and report results for each sex separately. The last two analyses mentioned are underpowered and cannot provide base for stating individual drug non-inferiority but could provide information of interest for future trial designs.

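### A sex main effect adjusts for sex but cannot show whether the treatment effect differs by sex; a small exploratory contrast and a rewording would fit the stated aim (minor)

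*Protocol article*

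**What the plan says.** Sequence generation {16a} gives the reason for stratifying: "We have chosen to stratify by sex because of diverging results in some previous trials for males [37] and females [41"]. The authors are not sure that the relationship is real, and add that "it is something that we would like to evaluate as a fixed effect in the primary analysis".

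Treatment duration describes what diverged. On one side: "A 7-day course of ciprofloxacin has been shown to be non-inferior to a 14-day course in women in an RCT [37"]. On the other, a more recent trial, cited directly after one in men, found that "a 7-day course of ciprofloxacin was inferior to a 14-day course of ciprofloxacin in short-time follow-up (10–18 days").

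Statistical methods for primary and secondary outcomes {20a} specifies a GEE model with identity link and binomial family, "with site as a random effect and sex as a fixed effect". No treatment-by-sex term is mentioned.

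Methods for additional analyses {20b} closes its list of five sensitivity analyses with "Lastly, we will analyse and report results for each sex separately". It then says of the control-drug and sex analyses: "The last two analyses mentioned are underpowered and cannot provide base for stating individual drug non-inferiority", and offers them as information for future trial designs.

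**The concern.** The findings said to diverge are treatment contrasts: 7 against 14 days of ciprofloxacin. The more natural reading of the stated aim is therefore whether a treatment effect differs by sex. The question has some relevance here, because Intervention description {11a} gives ciprofloxacin controls different durations by sex while the intervention lasts 10 days in both, so the contrast under study is not identical in men and women.

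A main effect of sex compares cure between women and men over both arms and imposes one common risk difference. The method named does not serve that aim. The separate analyses come closer, but with no stated comparison between them, the only yardstick in the article is the -10% rule of the primary analysis. One interval that clears -10% beside one that does not is not evidence that the sexes differ.

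**Working it through.** **Inputs from the protocol article.** Cure rate: "We expect a clinical cure rate of 93" per cent, taken as equal in both arms. Margin 10 points, one-sided alpha 2.5%, 300 evaluable patients, 30 clinics, intraclass correlation 0.1 (Sample size {14}); 1:1 allocation (Trial design {8}).

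**Assumption.** The article gives no sex split. The range 50:50 to 30:70 is used.

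**1. The plan's own figure.** Without clustering and with 150 per arm, SE = √(2 × 0.93 × 0.07 / 150) = 0.0295, and power = Φ(0.10/0.0295 − 1.96) = 92.4%. A simulation with 30 clinics of 10 patients, a random clinic intercept (correlation 0.1 on the latent scale), and identity-link GEE with constant working variance and sex as a fixed effect gave 89.4% (93% cure in the typical clinic) to 91.7% (93% cure overall). The stated 90% is reproduced.

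**2. What the main effect can and cannot show.** Take 75 patients per cell and weight the sexes equally. Suppose cure (PAC v control) is 88% v 93% in men and 98% v 93% in women.

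- The risk differences are −5 and +5 points, a 10-point interaction.
- The common risk difference is (−5 + 5)/2 = 0.
- The sex coefficient is (98 + 93)/2 − (88 + 93)/2 = 5 points.

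A trial with 90.5% cure in both arms for men and 95.5% in both arms for women gives the same pair, 0 and 5. The model has no term that separates the two situations. In simulation of the first, non-inferiority was declared in 93% of runs.

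**3. Separate analyses when the sexes do not differ.** With 93% cure in every cell and a 50:50 split (75 per arm per sex):

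- SE per sex = √(2 × 0.93 × 0.07 / 75) = 0.0417
- Probability of clearing −10% = Φ(0.10/0.0417 − 1.96) = Φ(0.44) = 67%
- Exactly one sex clears it: 2 × 0.67 × 0.33 = 44%

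| Sex split | Probability per sex | Both | Exactly one | Neither |
|---|---|---|---|---|
| 50:50 | 67%, 67% | 45% | 44% | 11% |
| 40:60 | 57%, 75% | 43% | 46% | 11% |
| 30:70 | 46%, 81% | 37% | 53% | 10% |

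The clustered simulation, with an even split overall, gave 42% to 45% for exactly one. Among trials that were non-inferior overall it was 42% to 47%.

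**4. The direct contrast.** SE of the difference between the two risk differences = √(2 × 0.93 × 0.07 × (1/n_men + 1/n_women)), with n per arm. At 50:50 this is √(0.1302 × 2/75) = 0.0589, and the 95% half-width is 1.96 × 0.0589 = 11.5 points.

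| Sex split | SE (points) | 95% half-width (points) | Power for a 10-point difference |
|---|---|---|---|
| 50:50 | 5.9 | 11.5 | 40% |
| 40:60 | 6.0 | 11.8 | 38% |
| 30:70 | 6.4 | 12.6 | 34% |

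**The case against.** The other side has four fair arguments.

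- **The sentence may mean prognosis.** Sequence generation {16a} never speaks of a differing treatment effect, and balancing a factor and then adjusting for it is how a prognostic factor is handled. On that reading the main effect is enough. The divergent trials also compared durations of ciprofloxacin, not PAC with control. This reading cannot be excluded, though the trials cited reported treatment contrasts and so point the other way.
- **Sex-specific results are already planned.** A reader might infer that the plan leaves the sex question unanswerable. It does not: two independent risk differences with intervals can be subtracted by hand. What is absent is a stated comparison.
- **No verdict by sex is planned.** A reader might also infer that the trial will probably report a false sex difference. No section declares non-inferiority by sex, and both analyses are labelled underpowered. The 44% applies only if someone uses the margin within each sex. On the effect scale, a chance gap above 10 points between the two estimates occurs in about 9% of trials at 50:50. The caveat on what may be concluded does, however, name only individual drugs.
- **An interaction term is often left to the analysis plan.** That is so, and its absence alone would be no fault. The point rests on the wording of {16a}, which names a method for its aim, and on a cheap improvement to an analysis that {20b} already states.

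**Conclusion.** The point holds as a minor one. On the more natural reading of its aim, the protocol names a term that cannot serve it, and the separate analyses have no stated comparison to guide their reading. If the margin were applied by sex, a split verdict would arise by chance in about 44% of trials at 50:50 and up to 53% at 30:70. These figures rest on 93% cure in every cell, 300 evaluable patients and an assumed sex split.

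Stratification by sex and adjustment for it are sound. Differences by sex are not among the listed objectives. The primary estimate, the margin, the decision rule and the sample size are unaffected, so nothing here supports reading the point as a flaw in the primary analysis.

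**What to change.** 1. In Sequence generation {16a}, keep the stratification and the sex main effect, and describe the latter as adjustment for a stratification factor. While editing, check the two reference numbers: {16a} attaches [37] to males and [41] to females, whereas Treatment duration attaches [37] to women and places [41] in its discussion of men.
2. In Methods for additional analyses {20b}, add an exploratory treatment-by-sex contrast on the risk-difference scale, reported as an estimate with its 95% interval.
3. In the same section, state that the sex-specific results are read through that interval and not by whether each clears −10%.

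The contrast will be imprecise, and its interval will show that openly. The cost is one extra model term outside the primary analysis and a few sentences, with no additional patients or data. It is best settled before the allocation code is revealed.
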